## Methods and study design

### Aims of the study

The primary objectives of this study are:To investigate whether tumor molecular markers can predict the response to irinotecan-based systemic treatment and are associated with QoL and OS;To validate the safety of *UGT1A1* genotype-guided dose adaptation (70% dose intensity) in UGT1A1 PMs;To assess whether high bacterial GUS enzyme activity is associated with irinotecan-induced GI toxicity, decreased QoL and OS

The most important secondary objectives of this study are:To investigate the dynamics in GUS activity and overall gut microbiota composition, diversity and functional capacity during irinotecan-based systemic treatment;To assess associations between GUS activity and gut microbiota composition, diversity and functional capacity,To measure fecal levels of SN-38 and SN-38-G and to determine its association with gut microbiota composition, bacterial GUS activity, *UGT1A1* genotype, treatment response and toxicity;To correlate tumor molecular profile, GUS activity and other clinical characteristics (e.g. physical performance and nutritional status) during irinotecan-based systemic treatment.

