#### Questionnaires

During the study period, patients are asked to fill out questionnaires at T1, T5, and T6 (Table 1). Amongst others, the questionnaires encompass questions concerning medical history, comorbidities, dietary patterns, the use of pre-/probiotics, the use of antibiotics and other co-medication, smoking, and alcohol use. Furthermore, patients are asked to score their physical functioning (based on the Karnofsky Performance Score, KPS), the risk of malnutrition (based on the MUST), as well as the occurrence of systemic and gastrointestinal toxicity (based on the CTCAE criteria, version 5.0 [24]). Furthermore, the European Organization for Research and Treatment of Cancer (EORTC) QLQ-C30 and the EQ-5D-5L questionnaires are used to quantify QoL.

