#### Statistical and bioinformatic analysis of main outcome parameters

The association between CMS subtypes 1–4 and treatment response (categorized as progressive disease, stable disease, partial response and complete response) will be analyzed using chi-squared tests. Survival analysis within the different CMS subtypes will be done by Kaplan Meier curves.

To validate the safety of the 70% irinotecan starting dose intensity, toxicity in UGT1A1 PMs will be compared to historical control patients, i.e. cohorts of patients described in literature that are homozygous polymorphic for *UGT1A1*28* and were treated with full dose therapy. In addition, toxicity in UGT1A1 PMs will be compared to UGT1A1 non-PMs treated with full dose in the current study, under the assumption that these groups experience comparable degrees of toxicity.

Correlations between GUS activity and the degree of experienced late-onset GI toxicity during irinotecan-based treatment will be analyzed by means of the Spearman correlation coefficient. Furthermore, we will investigate whether GUS activity is different between patients without diarrhea vs. grade 1–2 diarrhea vs. grade 3–4 diarrhea by means of ANOVA or the Kruskal Wallis test, depending on whether the data are normally distributed or not. Longitudinal changes in GUS activity during irinotecan-based treatment will be analyzed using repeated-measures ANOVA or the Friedman test.

Bioinformatic analysis of the predicted GUS functionality derived from metagenomics sequencing will be conducted. A Hidden Markov Model (HMM)-profile will be made per orthologous group with predicted GUS functionality, based on a reference dataset of publicly available GUS protein sequences and the results of Pollet et al. [12, 26]. The HMM-profiles will be used to identify all predicted proteins with a potential GUS functionality per fecal sample. These predicted proteins will be used to create a non-redundant microbial GUS protein catalogue.

Changes in GUS activity and overall gut microbiota composition, diversity and potential GUS capacity during irinotecan-based systemic treatment will be assessed by redundancy analysis (RDA) [27] and ANOVA [28]. These data will be used to examine the microbial GUS variation and origin per fecal community in order to link the microbial composition and GUS functional potential to the measured GUS activity.

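### The GUS–diarrhea tests take no account of diarrhea already present at T1, although the objective is irinotecan-induced toxicity and the T1 grade appears to be collected

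*Protocol article*

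**What the plan says.** The third primary objective in the protocol article (Aims of the study) reads "To assess whether high bacterial GUS enzyme activity is associated with irinotecan-induced GI toxicity, decreased QoL and OS".

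The section on statistical and bioinformatic analysis of main outcome parameters gives two analyses for its toxicity part. The first is a Spearman analysis of "Correlations between GUS activity and the degree of experienced late-onset GI toxicity during irinotecan-based treatment". The second asks whether "GUS activity is different between patients without diarrhea vs. grade 1–2 diarrhea vs. grade 3–4 diarrhea", to be tested "by means of ANOVA or the Kruskal Wallis test, depending on whether the data are normally distributed or not". Neither sentence names a baseline reference, a stratum or a covariate.

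Under Questionnaires, "patients are asked to fill out questionnaires at T1, T5, and T6", and patients score "the occurrence of systemic and gastrointestinal toxicity (based on the CTCAE criteria", version 5.0). One content list covers all three time points. According to Sampling time points, the baseline questionnaires and the first fecal sample both precede treatment.

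The exclusion criteria (Study population) list an ileostomy, but not diarrhea at baseline. Other systemic treatment is barred only within one month before inclusion, and abdominal radiotherapy only within two weeks.

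**The concern.** Induced diarrhea means diarrhea that arises or worsens because of the drug. The planned groups are defined by recorded grade alone. A patient with advanced disease, previous bowel surgery or recent treatment may have loose stools before the first dose. If these persist, the patient can fall in a diarrhea group for reasons unrelated to irinotecan.

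That alone adds noise. It becomes bias if T1 diarrhea is also related to the GUS measurement. This is plausible, because activity is measured in fecal lysate, and the Discussion wants to identify patients at risk before treatment starts, which makes the T1 sample a natural predictor. T1 diarrhea would then be linked to both predictor and outcome. Depending on the direction of the link, the tests could report an association with no irinotecan effect behind it, or lose a real one.

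**Working it through.** The plan states no figure for this point, so there is none to reproduce. The mechanism can be checked by simulation.

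**Inputs from the article (Sample size calculation).** Evaluable patients: 84. Diarrhea of any grade: 82%. Grade 3–4: 18%. Hence no diarrhea 100 − 82 = 18%, and grade 1–2 82 − 18 = 64%.

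**Assumptions, not in the documents.** T1 diarrhea in 10–30% of patients. Mean GUS activity in those patients shifted by 0, 0.5 or 1 SD. Two carry-over rules:
- additive: recorded category = min(induced category + 1, highest category) for patients with T1 diarrhea;
- maximum: T1 diarrhea only turns no diarrhea into grade 1–2.

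**Model.** GUS = e + shift × (T1 diarrhea), with e standard normal. The induced grade comes from a latent normal variable, cut to give 18/64/18% and correlated with e at 0 (no true effect) or 0.35. Tests at 5%. Spearman: 4,000 trials per setting, Monte Carlo standard error at 5% √(0.05 × 0.95/4000) = 0.3 points. Kruskal-Wallis: 1,500 trials, √(0.05 × 0.95/1500) = 0.6 points.

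**False-positive rate, no true effect, additive carry-over**

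| T1 diarrhea | GUS shift | Spearman | Kruskal-Wallis (higher / lower GUS) |
|---|---|---|---|
| 10% | 0.5 SD | 8.3% | 6.5% / 9.1% |
| 10% | 1 SD | 16.0% | 14.9% / 16.2% |
| 20% | 0.5 SD | 13.7% | 12.6% / 12.5% |
| 20% | 1 SD | 39.6% | 33.2% / 36.2% |
| 30% | 0.5 SD | not run | 17.6% / 17.1% |
| 30% | 1 SD | not run | 54.0% / 49.7% |

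Over repeat runs the Spearman range is about 7–41%.

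**Where there is no inflation.** With no GUS shift, Kruskal-Wallis gives 4.6–6.1%. Under the maximum rule, Spearman gives 4.9–6.6% even with a shift.

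**Hiding a real effect (Kruskal-Wallis, latent correlation 0.35, additive carry-over).** Restricted to patients without T1 diarrhea, power is 0.50–0.67. In the analysis as written it is 0.15–0.42 when T1 diarrhea goes with lower GUS, and 0.77–0.98 when it goes with higher GUS. With no shift the loss is 4–7 points (0.604 to 0.560, 0.587 to 0.519 and 0.515 to 0.462 at 10, 20 and 30% prevalence).

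**Remedies compared**
- Partial Spearman, r(xy·z) = (r_xy − r_xz r_yz)/√[(1 − r_xz²)(1 − r_yz²)], with x = GUS, y = recorded grade and z = T1 diarrhea: false-positive rate 4–6% in every setting, power 0.73–0.79.
- Restriction to patients without T1 diarrhea (Kruskal-Wallis): false-positive rate 4–6%. Power falls with the patients lost: 0.60–0.67, 0.58–0.60 and 0.50–0.52 at 10, 20 and 30% prevalence.
- Recoding anyone not above the T1 grade as having no diarrhea: false-positive rate 6–28% under additive carry-over and 8–29% under the maximum rule, where the unadjusted test was nearly nominal. The recoding moves patients with T1 diarrhea, and their shifted GUS values, into the no-diarrhea group.

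**The case against.** The strongest reply is that a condensed article need not say how each patient's grade is derived, and that a full protocol or SAP may handle baseline symptoms. That is fair as to derivation. A reader might infer that the plan counts pre-treatment diarrhea as toxicity; no passage says so, and that reading should not be pressed. What stands is narrower: the article fixes the groups and unadjusted tests for a primary objective about induced toxicity.

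Second, the Spearman sentence is already limited to late-onset toxicity during treatment, and the group comparison can be read the same way. This limits timing only. Diarrhea present at T1 that persists is still included.

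Third, on-treatment grades may already be scored relative to the patient's baseline. The documents do not say. If they are, the problem narrows, and one sentence would settle it.

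Fourth, collection of the T1 grade is inferred from a single content list, while Sampling time points distinguishes baseline from follow-up questionnaires. It is the natural reading, but not certain.

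Fifth, the larger rates rest on strong assumptions. A reader might take 40% as the expected error rate; the documents do not support that. It needs 20% prevalence, a 1 SD shift and every affected patient raised a full category. That model records 18 + 0.20 × 64 = 30.8% grade 3–4 (18 + 0.10 × 64 = 24.4% at 10% prevalence), above the planned 16–22%. Recalibrating to 18% recorded grade 3–4 at 20% prevalence does not remove the inflation (20% at 0.5 SD, 58% at 1 SD), but leaves only about 3% grade 3–4 due to irinotecan alone, which no passage supports.

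Lastly, the sample-size aim is prediction, for which the absolute on-treatment grade is a defensible outcome. This is a reason to keep the unadjusted analysis alongside the adjusted one.

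The article also has partial safeguards: exclusion of ileostomy and of recent antibiotics and radiotherapy, planned correlations with other questionnaire variables, and a general caveat on medical history. None addresses baseline diarrhea.

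**Conclusion.** The concern holds in a conditional form. The GUS–toxicity tests are unadjusted, the objective is induced toxicity, T1 diarrhea is not excluded, and a T1 grade appears to be available but is not used. Bias in the false-positive rate needs two things together: T1 diarrhea related to measured GUS, and T1 diarrhea carried into the on-treatment grade by more than turning none into grade 1–2. Without both, the rate stays at about 5%; with no GUS shift, additive carry-over costs only a few points of power. With both, at shifts of 0.5–1 SD and 10–20% prevalence, the Spearman rate is about 7–41%. These figures show what could happen; they do not estimate what will.

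A reader might also infer that the outcome should become the grade above T1, with everyone else counted as having none. The simulations do not support this, since that recoding itself biases the comparison. The point merits a change because adjustment protects against the bias at almost no cost, not because a large bias has been shown.

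**What to change.** 1. Make the main GUS–toxicity analysis one adjusted for T1 diarrhea grade: a partial Spearman correlation, or an ordinal logistic model of on-treatment grade (none, 1–2, 3–4) on GUS activity with T1 grade as covariate.
2. Keep the unadjusted Spearman and ANOVA/Kruskal-Wallis tests as supportive analyses.
3. Add a sensitivity analysis restricted to patients without diarrhea at T1.
4. State whether on-treatment grades are scored relative to T1, and confirm that the T1 questionnaire includes the diarrhea item.
5. Do not recode patients who do not exceed their T1 grade as having no diarrhea.

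If the T1 questionnaire carries the item, as the Questionnaires section reads, the cost is wording only: no extra patients, visits or samples. If it does not, a baseline bowel item must be added, or taken from the medical records that the article already plans to use to complete questionnaire data. The choice should be fixed before GUS results are linked to toxicity.

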#### Sampling time points

The sampling period encompasses the first six cycles of irinotecan-based systemic treatment. Before treatment initiation, patients will collect the first (baseline) fecal sample and fill out baseline questionnaires. Additionally, routine computed tomography (CT) or magnetic resonance imaging (MRI) scan as well as *UGT1A1* genotyping will be conducted. Afterwards, patients will enter the regular treatment cycles of irinotecan-based systemic treatment. During the first six cycles, they will regularly collect fecal samples and complete follow-up questionnaires (Table 2). The exact number of weeks between sampling time points might vary, depending on the treatment regimens and potential treatment delays. If available, archived tumor tissue will be used for molecular tumor profiling.

**Table 2 Tab2:** Sampling timepoints of the OPTIMA study

		**Inclusion**	**Baseline**	**Cycle 1**	**Cycle 2**	**Cycle 3**	**Cycle 4**	**Cycle 5**	**Cycle 6**
Regular treatment	Hospital visit	X	X	X	X	X	X	X	X
	Archived tumor tissue		X						
	CT/MRI		X				X		
	Blood sample for UGT1A1		X						
Study related	Questionnaires		T1				T5		T6
	Fecal sample		T1	T2	T3	T4	T5		T6

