### Statistical and bioinformatic analyses

#### Sample size calculation

The sample size calculation was based on having sufficient precision to estimate sensitivity and specificity of the GUS activity assay to predict late-onset GI toxicity. Literature shows that about 82% of patients treated with irinotecan experience diarrhea (all grades) [25], while approximately 18% develop grade 3–4 diarrhea [5, 6]. For estimation of sensitivity, we determined a maximum half-width of the 95% confidence interval (CI) of 17%, requiring a minimum of 22 patients with grade 3–4 diarrhea. To achieve this precision, a total of 84 patients need to be included, considering an estimated toxicity rate ranging from 16 to 22%. Out of these 84 patients, 62 individuals would not experience grade 3–4 diarrhea, allowing for the estimation of specificity with a 95% CI half-width of around 10%. Hence, the total number of patients required remains at 84. Considering an anticipated 20% drop-out rate, because of the advanced setting, 104 patients need to be included in the study.

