## Discussion

To the best of our knowledge, the OPTIMA study will be the first study to evaluate tumor molecular profiling, *UGT1A1* genotype and GUS activity as potential biomarkers for efficacy and toxicity of irinotecan-based systemic treatment in patients with advanced CRC. By combining these three biomarkers into one study, we will provide pivotal new insights for clinicians to make well-considered choices concerning for instance the initiation, dose adjustments or the need for microbiota modulation during irinotecan-based systemic treatment in this patient population.

The tumor molecular profiling will provide new insights into which patients are expected to benefit from irinotecan-based systemic treatment. As outlined in the introduction, irinotecan-based systemic treatment is probably not the optimal choice in all CMS subtypes. Validation of these previous findings in the current cohort will significantly strengthen the rationale for a more personalized treatment selection based on the tumor molecular profile.

Furthermore, OPTIMA will further evaluate the use of *UGT1A1* genotype and subsequent dose adjustments in clinical practice. If a 70% dose intensity in UGT1A1 PMs leads to similar incidences of severe toxicity as compared to UGT1A1 NMs and IMs treated with the full dose, this further supports the validity and utility of this biomarker.

In addition, new knowledge on the role of bacterial GUS in a clinical setting, will enhance the detection of patients who are expected to experience high GI toxicity before start of the treatment. This opens the opportunity to modulate GUS activity in these patients by targeted gut microbiota modulation.

However, there are some limitations inherent to the current study. Due to the inclusion of patients receiving different treatment regimens, as well as potential treatment delays in individual patients, the time between two consecutive sampling time points might differ between patients. Additionally, we only ask patients to report overall dietary patterns and do not collect detailed data on dietary intake, which might influence particularly the gut microbiota parameters. Lastly, due to the advanced setting, patients might have distinct and complex medical histories, co-morbidities and co-medication which could influence the outcomes.

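### The tests fixed for longitudinal GUS activity use only patients with every sample entered and ignore sampling time; a mixed model would use all samples

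*Protocol article*

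**What the plan says.** The section on statistical and bioinformatic analysis of main outcome parameters names the method for GUS activity over time: "Longitudinal changes in GUS activity during irinotecan-based treatment will be analyzed using repeated-measures ANOVA or the Friedman test". The article names no other model for this question. The aims section lists the dynamics of GUS activity during treatment first among the secondary objectives.

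Table 2 schedules six fecal samples per patient: T1 at baseline, T2 to T5 at cycles 1 to 4, and T6 at cycle 6. Patients collect and freeze them at home.

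Three other places bear on how complete and how regular these series will be:

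- Sample size calculation: "Considering an anticipated 20% drop-out rate, because of the advanced setting, 104 patients need to be included in the study".
- Background: severe toxicity frequently results in a lower irinotecan dose or in treatment being stopped early.
- Sampling time points and Discussion: spacing depends on regimen and delays, so that "the time between two consecutive sampling time points might differ between patients".

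**The concern.** Classical repeated-measures ANOVA and the Friedman test both work on complete blocks. A patient who lacks one of the time points entered contributes nothing, even if the other samples were collected and assayed. Samples T2 to T6 are tied to treatment cycles, so a patient who stops early will normally have an incomplete series. Home collection makes isolated gaps likely as well.

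The loss may not be neutral. The study's hypothesis is that high GUS activity goes with gastrointestinal toxicity, and the Background links severe toxicity to early stopping. If both hold, patients with all samples are partly selected on the variable being measured, and the early samples of those who stop are left out of the longitudinal analysis.

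Neither test uses the date of sampling, and Friedman cannot adjust for regimen, although cycle length differs by regimen (Table 1). At stake are the precision and representativeness of a secondary objective. The Discussion counts repeated sampling per patient among the study's particular strengths.

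**Working it through.** **Inputs from the Protocol article:** 84 evaluable patients, 104 enrolled and 20% drop-out (Sample size calculation); six samples (Table 2); cycles of 2 or 3 weeks (Table 1).

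**Assumed input:** m, the chance that any single sample is missing in a patient who stays in the study, independent between samples. The article gives no value, so a range of 0 to 15% is shown.

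**1. The plan's own figure.** The article says "Hence, the total number of patients required remains at 84" before drop-out. Then 84 / (1 − 0.20) = 105, against the stated 104, a difference of one patient. In the other direction, 104 × 0.80 = 83.2. Drop-out alone therefore leaves about the planned number.

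**2. Patients with complete series.** With k time points entered in the test:

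complete = 104 × 0.80 × (1 − m)^k

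| m (assumed) | k = 6 | share of 104 | k = 3 |
|---|---|---|---|
| 0% | 83.2 | 80% | 83.2 |
| 2% | 73.7 | 71% | 78.3 |
| 5% | 61.2 | 59% | 71.3 |
| 10% | 44.2 | 43% | 60.7 |
| 15% | 31.4 | 30% | 51.1 |

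For example, 0.80 × 0.95^6 = 0.588, and 0.588 × 104 = 61; 0.80 × 0.90^6 = 0.425, and 0.425 × 104 = 44. At m = 5%, about 83 − 61 = 22 patients who stayed in the study would be excluded for at least one gap; at m = 10%, about 83 − 44 = 39. Entering three time points instead of six keeps more patients but sets aside the other three samples of each. A likelihood-based mixed model keeps every patient with at least one sample, up to 104.

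**3. Timing.** Six cycles span 6 × 2 = 12 weeks with FOLFIRI or FOLFOXIRI and 6 × 3 = 18 weeks with monotherapy, before any delay. The same label, T6, therefore stands for different elapsed times.

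**4. Size of a possible bias.** An illustrative simulation used 150 runs of 104 patients, a random patient intercept, a true rise of 0.50 from T1 to T6, and a total SD of about 1. Drop-out depended on the previous GUS value and left about 18% of patients incomplete. All parameters were assumed.

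| | Truth | Complete cases | Mixed model |
|---|---|---|---|
| Mean at T1 | 0.00 | −0.12 | −0.02 |
| Mean at T6 | 0.50 | 0.41 | 0.50 |
| Change | 0.50 | 0.53 | 0.51 |

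Complete-case levels were about 0.1 SD too low, while the change was nearly right under both methods. All simulated patients shared the same underlying trend, so the exercise does not address selection on patient-specific trends.

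**The case against.** The strongest reply is that the harm is modest and partly hypothetical. The article is a condensed account: it does not say that all six samples enter one test or how gaps are handled, and such detail may sit in a full protocol or analysis plan that is not shown. The 20% drop-out is already built into the 104. The objective is secondary and did not size the study. The main GUS and toxicity comparisons use Spearman correlation and ANOVA or Kruskal-Wallis, which need no complete series, so early samples from patients with toxicity are not necessarily lost to the study. A mixed model brings assumptions of its own.

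Most of this stands, and it limits the point. It does not remove it, because the article fixes the choice of test, and exclusion of incomplete series is how those tests ordinarily work.

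A reader might also infer several stronger things that the article does not support:

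- That the expected drop-out is due to toxicity or progression. The only reason given is the advanced setting, and patients whose dose is reduced during treatment may stay in the study.
- That the tests assume equally spaced visits. They treat time as unordered categories; they ignore spacing and do not assume it. Cycle is also a legitimate time axis.
- That the redundancy analysis and ANOVA of microbiota change treat repeated samples as independent. The article is silent on this, and silence in a condensed article is no evidence.

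**Conclusion.** The point holds as one of efficiency and possible selection in a secondary objective. With drop-out alone, at most about 83 of 104 patients have all six samples, which is no shortfall against the plan. Any further loss comes from intermittent gaps: about 61 or 44 complete patients at an assumed, independent 5% or 10% loss per sample, if all six time points are entered together. No figure in the article supports a particular rate.

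That the loss is related to GUS activity is plausible from the study's hypothesis and Background, but it is an inference. It would be tempting to conclude that the estimated change in GUS activity will be badly biased. That is not shown: the illustration gave shifted levels and a nearly correct change. The supported costs are lost patients, a possibly selected subset, and disregard of sampling time that the article itself says will vary.

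**What to change.** Replace the two named tests with a linear mixed model on suitably transformed GUS activity that uses all available samples from T1 to T6. Include a random intercept per patient, cycle (or actual time since the start of treatment) as a fixed effect, and regimen as a covariate. State that the analysis assumes data are missing at random given the observed values. Keep the Friedman test on complete cases as a sensitivity analysis, and report how many patients each analysis uses.

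The cost is a change of wording and slightly more analysis work in standard software, with no extra patients, samples or visits. The downside is reliance on the missing-at-random and distributional assumptions; the retained Friedman test gives a check on the second.

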## Background

Colorectal cancer (CRC) represents a major public health concern as it is the third most frequently diagnosed cancer and the second cause of cancer-related mortality worldwide [1]. In 2022, 21% of patients with newly diagnosed CRC in the Netherlands suffered from metastatic disease [2]. In this group of patients, irinotecan-based systemic treatments are commonly applied to relieve symptoms, improve quality of life (QoL) and extend overall survival (OS).

However, the individual response to irinotecan-based treatment differs consistently between patients, and is currently largely unpredictable. Previous research indicated that molecular tumor characteristics might be associated with response to irinotecan-based systemic treatment. CRC can be subdivided into four consensus molecular subtypes (CMS1-4), based on different gene expression profiles [3]. Ten Hoorn et al. concluded based on a meta-analysis that specifically in CMS4 metastatic disease, patients benefit more from irinotecan-based regimens compared with oxaliplatin-containing regimens [4].

An additional disadvantage of irinotecan-based systemic treatment is the occurrence of systemic (primarily neutropenia) and late-onset gastrointestinal (GI) toxicity, (primarily diarrhea). For instance, grade 3–4 neutropenia has been previously identified in 46% and grade 3–4 diarrhea in approximately 18% of patients [5, 6]. The occurrence of severe toxicity often leads to irinotecan dose reduction, or premature discontinuation of the treatment. This negatively affects not only the patient’s QoL and OS, but also puts significant pressure on family and caregivers, as well as on hospitalization-related healthcare costs [7]. Consequently, there is an urgent need for biomarkers to identify patients at risk for developing irinotecan-induced toxicity. In this context, two promising candidate biomarkers are 1) the UDP Glucuronosyltransferase Family 1 Member A1 (*UGT1A1*) genotype of the patient and 2) the microbial enzyme β-glucuronidase (GUS).

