#### Quantification of bacterial GUS activity and gut microbiota composition in fecal samples

Fecal samples will be collected at home using a patient-friendly, and easy-to-use collection kit. At each time point, patients are asked to fill two fecal collection tubes with spoons attached to the lid (Sarstedt, Nümbrecht, Germany) and to immediately store samples in a freezer at home, until their next hospital visit. Cooled transporter container (Sarstedt, Nümbrecht, Germany) will be provided to the patients to ensure that the samples remain frozen during the transport to the hospital. Upon arrival in the hospital, samples will be temporarily stored at −20°C and at −80°C for long-term storage.

GUS activity in these samples will be quantified using an enzyme activity assay, which is based on the assay as described by Jariwala et al. and Bhatt et al. [15, 18] and which is currently under validation in our laboratories for the use with human fecal samples. In short, this assay consists of three steps: firstly, a pre-processing to remove unwanted debris, secondly a bicinchoninic acid (BCA) assay (Pierce™ BCA Protein Assay Kit, Thermo Fisher Scientific, USA) to determine the total protein concentration in the fecal lysate, and thirdly a fluorescence-based enzyme activity assay quantifying SN-38G-specific GUS activity. For the enzyme activity assay, fluorescent SN-38G is added to the fecal lysate and conversion to SN-38 during a period of one hour is quantified using a SpectraMax iD3 multi-mode microplate reader (Molecular Devices, San Jose, CA, USA). Subsequently, an online algorithm-based calculation tool (developed by the University of North Carolina, USA) will be used to calculate SN-38 reactivation rate as concentration over time (nM/min). Fecal levels of SN-38 and SN38-G will also be measured directly in fecal samples by means of a liquid chromatography-mass spectrometry (LC–MS/MS) assay.

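### The longitudinal GUS analysis uses complete-block tests that drop every patient with an incomplete stool series; a mixed model would use all collected samples at almost no cost.

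*Protocol article*

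**What the plan says.** The Protocol article, under Statistical and bioinformatic analysis of main outcome parameters, fixes the method: "Longitudinal changes in GUS activity during irinotecan-based treatment will be analyzed using repeated-measures ANOVA or the Friedman test". The sentence does not list the time points. Table 2 (Sampling time points) schedules six stool samples: T1 at baseline, T2 to T5 in cycles 1 to 4, and T6 in cycle 6. The section on quantification of GUS activity then says: "GUS activity in these samples will be quantified using an enzyme activity assay". Only the metagenomic sequencing is limited to T1, T2 and T5. That the test spans all six samples is therefore an inference, but it is the natural one.

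Two other statements bear on how many series will be complete. Sample size calculation: "Considering an anticipated 20% drop-out rate, because of the advanced setting, 104 patients need to be included in the study". Background: "The occurrence of severe toxicity often leads to irinotecan dose reduction, or premature discontinuation of the treatment". The text shown names no imputation, mixed model or other handling of incomplete series for this analysis. Under Aims of the study, the dynamics of GUS activity during treatment are the first-listed secondary objective.

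**The concern.** Classical repeated-measures ANOVA and the Friedman test both work on complete blocks. A patient who misses one sample, or who stops before cycle 6, is removed with all the samples already collected and assayed. The plan itself predicts that some series will be incomplete, and home collection of stool makes occasional gaps plausible as well.

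Two things are at stake. Early changes, such as T1 to T2, are estimated from fewer patients than actually supplied both samples. The time course also describes only patients who completed the series. If stopping is related to earlier GUS values, those patients may not represent the cohort. In addition, the Friedman test alone gives an overall p-value, whereas an objective about dynamics calls for the size and direction of change at each time point.

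**Working it through.** **The plan's own figure.** 84 / (1 − 0.20) = 105, against 104 stated, which agrees to within one patient. In reverse, 104 × 0.80 = 83.2.

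**Inputs.** From the documents: N = 104, drop-out d = 0.20, six scheduled samples. Assumed: drop-out means no sample at T6 and is spread evenly over the five intervals; each remaining stool is missed independently with probability m. The documents give no value for m, so m = 0 is the only case that rests on their figures.

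**Formulas.**
- Complete patients: 104 × (1 − d) × (1 − m)^6
- Samples collected: 104 × (1 − m) × Σ(1 − d·k/5), for k = 0 to 5
- Share discarded: 1 − 6 × complete patients / samples collected
- T1–T2 pairs available: 104 × (1 − d/5) × (1 − m)^2
- Standard-error ratio for T1–T2, complete cases against all available pairs: √(pairs available / complete patients)

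**Drop-out only (m = 0).**
- Complete: 104 × 0.80 = 83.2, so about 21 patients are removed.
- Collected: 104 × (1 + 0.96 + 0.92 + 0.88 + 0.84 + 0.80) = 104 × 5.4 = 561.6.
- Used: 6 × 83.2 = 499.2. Discarded: 1 − 499.2 / 561.6 = 11.1%.
- T1–T2 pairs: 104 × 0.96 = 99.8. Standard-error ratio: √(99.8 / 83.2) = 1.095.

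**With missed stools as well (d = 0.20).**

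| m (assumed) | Complete patients | Samples collected | Discarded | SE ratio, T1–T2 |
|---|---|---|---|---|
| 0 | 83 | 562 | 11% | 1.10 |
| 0.02 | 74 | 550 | 20% | 1.14 |
| 0.05 | 61 | 534 | 31% | 1.21 |
| 0.10 | 44 | 505 | 48% | 1.35 |

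**Other drop-out rates, m = 0.** At d = 0.10: about 94 complete, 5% discarded, SE ratio 1.04. At d = 0.30: about 73 complete, 18% discarded, SE ratio 1.16.

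**Simulation check, random drop-out.** 300 simulated cohorts of 104, within-patient correlation 0.5 (assumed), no missed stools, complete cases against a random-intercept mixed model. The standard deviation of the T2–T1 estimate was 0.108 against 0.100. For T6–T1 it was 0.100 against 0.099. The precision gain is thus modest early and negligible at T6, because a patient without T6 adds little to that contrast.

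**Simulation check, stopping dependent on the last GUS value (assumed mechanism).** In the same set-up with a true T6–T1 change of 0.300, complete cases averaged 0.327 (9% too large) and the mixed model 0.307. A different set-up, with random intercepts and slopes and a true change of 0.40, gave 0.34–0.35 for complete cases (13–15% too small) and 0.39–0.40 for the likelihood analysis. The complete-case error changes sign with the assumptions. The likelihood estimate stayed close to the truth in both.

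**The case against.** The strongest objection concerns size. On the only attrition figure in the documents, nine-tenths of the collected samples are still used and the T1–T6 change loses almost no precision. The larger losses need an assumed rate of missed stools. This stands, and the point should lead with the 20%-only result. The 20% itself is attributed to the advanced setting and was set for the sensitivity and specificity estimate; reading it as the proportion without a T6 sample is a further assumption.

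A reader might infer that the complete-case time course is biased in a known direction, or that the deleted patients are those with high GUS activity. The documents support neither. A link between high GUS and toxicity is the hypothesis under study. Severe toxicity is said to lead to dose reduction or discontinuation, and patients on a reduced dose can still give samples. No GUS variance, correlation, trajectory or stopping mechanism is given.

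A reader might also infer that the primary GUS question is affected. It is not: association with late-onset GI toxicity has its own tests (Spearman, and ANOVA or Kruskal–Wallis). The same section also plans redundancy analysis and ANOVA for changes in GUS activity and the microbiota, so this sentence is not the only look at change over time.

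Finally, the article is condensed. An unseen analysis plan could add pairwise contrasts, effect estimates or imputation, so the omnibus nature of the Friedman test is a minor point. The article does, however, commit to two named tests that in standard form cannot use an incomplete series, and nothing else in it repairs that. Nor does the drop-out inflation: it restores numbers, not the deleted patients' data.

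**Conclusion.** The point holds as a cheap improvement to a secondary analysis. The named tests discard every patient with an incomplete series in a cohort where incomplete series are expected.

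On the plan's 20% alone, the cost is about 21 of 104 patients, about 11% of collected samples, a standard error about 10% larger for T1–T2 and almost nothing for T1–T6. With 5% or 10% of stools also missed, which is assumed and not documented, 31% or 48% of collected samples are lost. Bias is a real possibility if stopping depends on earlier GUS values, but its direction and size cannot be determined from the documents.

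The result rests on the six-sample reading of Table 2, even spread of drop-out, independently missed stools and the standard complete-block form of both tests.

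**What to change.** Replace the sentence with wording such as: longitudinal GUS activity, suitably transformed (for example log if skewed), will be analysed with a linear mixed model for repeated measures using all available samples, with time point as a fixed factor and a patient random effect or unstructured covariance; each time point will be compared with T1 and reported with a 95% CI. Keep repeated-measures ANOVA or the Friedman test only as a complete-case sensitivity analysis, and state that T1 to T6 are the time points.

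The cost is a sentence or two of analysis wording and standard software; no new data or visits are needed. The downside is that a covariance model must be stated and that the analysis relies on data being missing at random. That is weaker than the missing-completely-at-random condition behind the complete-block tests, but it would still fail if stopping depended on GUS values that were never observed.
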